### **Inclusion**

This trial relates to care practice. In order to meet the main objective, it requires homogeneity of intubation fixation practices within a given department during each of both inclusion periods, regardless of the status of the patient in the study (included or not).

Thus, in each ICU participating in the project, whatever the inclusion arm considered (A or B), all patients requiring invasive mechanical ventilation (MV) from their admission to the intensive care unit (if the respiratory assistance was set up before admission to the intensive care unit) or from the moment the respiratory assistance was set up (if it was set up in the intensive care unit), will benefit from the fixation method according to the inclusion arm (A or B) described above, whether they are included in the study or not. D0 is defined as the first day of the study fixation system of the ETT (cord + sheath or elastic adhesive bands).

Information and consent to participate in the study will be sought from patients requiring MV (or their relatives), who meet all the inclusion criteria and have no non-inclusion criteria (see chapter 3.3).

In the absence of the physical presence of the trusted support person or a relative, an emergency procedure will be available to include the patient. In all cases, the relative and then the patient will be informed as soon as possible by the investigator who will deliver the information note and the collection of their oral consent will be carried out secondarily by the investigator.

After having ensured the consent of the patient or his relatives or having followed the emergency inclusion procedure, the investigator can then include the patient before the D1 photograph. Moreover, if the information was initially given to the relatives, the consent will also be sought from the patient as soon as his level of vigilance allows it.

One of the criteria for non-inclusion of the patient is the presence of pre-existing facial lesions on arrival in the ICU in the path of the endotracheal tube fixation.

When the patient is admitted to the ICU already intubated, the tube is already fixed and this fixation is generally changed in order to put in place the fixation system used in the department. Within the framework of the protocol, we will ask that it be systematically changed to install the fixation system under study. The non-inclusion criterion can therefore be assessed at this point.

Assessment of the primary endpoint requires a photograph of the patient's mouth upon admission. The patient is often unconscious and/or unable to give consent. Relatives are not always present to be informed of the study and to give their consent. Waiting for the consent of the relatives requires removing the fixation system again after having obtained their consent in order to take the picture. This may result in additional skin damage. In addition, it is necessary to take the photo of each patient at the same time (admission) so that each patient has an initial photo with a comparable temporality. If relatives come 24 hours after admission, a lesion could possibly appear when there was none at admission.

We therefore propose to take a photograph of all intubated patients on admission and to delete this photograph from the device if the patient is ultimately not included in the FIXATUB study.

A follow-up table of patients likely to participate in the study will be kept up to date, noting the reasons for non-inclusion and objections to participation. This will be sent to the coordinating investigating center at the beginning of each month in a format that respects patients' anonymity.

## Follow-up

During the two recruitment periods, a logbook will be given to the paramedical staff and will include the follow-up of each change of fixation made during their stay in the ICU.

The notebook will also record the presence of vasopressors, prone positioning, extubation or re-intubation, or the presence of sedation, which are risk factors for injury in resuscitation patients.

The nurse in charge of the patient will have to change the fixation system at least once a day and if necessary during the day in case of soiling or examinations.

Duoderm-type dressings used to prevent pressure sores under the endotracheal tube will not be accepted, since this is the subject of the study. However, it can be applied as a curative measure if a lesion appears.

A verification of the correct positioning of the endotracheal tube thanks to the graduated marker will be systematically carried out once a day. If a repositioning is necessary the nurse will note the number of centimeters (either at the bottom or at the top). The mobilization of the tube (change of side) will be performed according to the usual practices of the service.

The number of mobilizations, interventions (e.g., retying the knot) on the fixation system and the number of fixation system changes will be recorded daily.

The presence or absence of lesions will be assessed daily by the nurse in charge of the patient. She will also assess the type of lesion: cutaneous or mucous and depending on the type will use the appropriate scale to assess the grade: NPUAP scale (cutaneous) or / and the ROMPIS scale (mucous).

Two photos (one with the lower lip visible and one with the upper lip visible) will be taken every day by the nurses from the day of the first fixation change = D0 until D10. In no case will the whole face of the patient be taken. The patient will not be identifiable. The photos will be taken without the fixation visible to allow the blind to be kept for the committee that will evaluate the photos. The photos will be identified only by the patient's number and the date.

Each expert will have to record the presence or not of a peri-oral lesion between D0 and D10 of maintenance of respiratory assistance via an endotracheal tube. .

For the primary endpoint, we selected a daily photo assessment until D10. The choice of this time frame was based on:

- the time of appearance of peri-oral lesions (more than 50% of them appear during the first 5 days) (7)

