#### **2.1.2. Primary endpoint**

Appearance of at least one peri-oral lesion during the first ten days of maintaining the orally inserted endotracheal tube.

The peri-oral lesion will be validated on photographs by an independent review committee. The photos will be taken daily, taking the precaution that the fixation system is not visible (maintaining the blindness for the adjudication committee) from D0 to D10.

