### **3.3. CRITERIA FOR NON-INCLUSION**

- Pre-existing facial lesions on arrival in the intensive care unit on the path of the endotracheal tube fixation
- Admitted intubated following transfer from another intensive care unit
- Nasotracheal intubation
- Patient in isolation for suspected COVID or clinically proven COVID
- Patient admitted with tracheostomy
- Pregnant, nursing and parturient women
- Lack of social security affiliation
- Moribund (High probability of death within 48 hours of inclusion)
- Incapacitated adult (under guardianship, curatorship)
- Patient deprived of liberty by court order

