#### Secondary criteria

The number of self-extubations, repositioning of the ETT will be estimated and compared using a Poisson regression model taking into account the study design. An offset of the logarithm of the intubation time will be included in the model.

The time to the first peri-oral lesion will be estimated using a random-effects survival model to account for the study design.

The time to onset will be calculated from the date of intubation to the date of first lesion onset. Patients for whom no lesion appeared will be censored at the date of extubation or at the date of discharge from intensive care or at D28. Patients who died will be censored at their date of death.

The grade of skin lesions (NPUAP scale) and mucosal lesions (Rompis scale) will be collected for each lesion. If the patient has no lesions, a grade=0 on the corresponding scale will be retained. If a patient presents several lesions, the maximum grade observed will be retained.

An ordinal logistic regression model controlling for intubation time and study design will be applied to compare both types of fixation.

The incidence of peri-oral lesions (expressed per 1000 ventilator days) will be calculated and described in each group: number of patients with at least one lesion / total number of ventilator days (up to 1ère lesions in patients with one lesion)

The maximum number of injuries per day will be estimated and compared using a linear model taking into account the study design.

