### **6.2.2. Statistical justification of the number of inclusions**

The study will take place in 16 centers (clusters) over two 12-month periods.

According to the IDEFIX study (7), we hypothesize that 35% of patients with a "cord and sleeve" fixation system have a peri-oral lesion compared to 20% with the elastic adhesive tape system.

The calculation of the number of subjects needed must take into account the design of the study and thus the two intra-class and inter-class correlation coefficients (15)

As we have no data on the estimation of correlation coefficients, we have retained, for the calculation of the number of subjects, a "moderate" intra-class correlation coefficient and therefore defined at 0.1, and as recommended, an inter-class correlation coefficient equal to half of the intra-class correlation coefficient, i.e. 0.05 (16)

With 90% power and 5% alpha risk, we calculated that each of the 16 centers would need to include an average of 24 patients per period.

A total of 768 patients are to be included.

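### The primary endpoint is the appearance of a lesion, but adjudicators record presence from D0, no rule discounts a lesion already on the D0 photo, and D0 is worded in two ways

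*Protocol*

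**What the plan says.** Protocol section 2.1.2 defines the primary endpoint as an incident event: "Appearance of at least one peri-oral lesion during the first ten days of maintaining the orally inserted endotracheal tube". The Follow-up part of section 4.3 sets a different task for the experts: "Each expert will have to record the presence or not of a peri-oral lesion between D0 and D10". Section 4.5.1 (Adjudication Committee) repeats that task. Each member receives the patient's whole photo file and rules on whether a lesion is present or absent. Neither place mentions a comparison with the D0 image.

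The Inclusion part of section 4.3 explains why a photograph is needed at admission: if the first picture were taken a day later, it might show a lesion that was not there on arrival. Section 3.3 excludes patients with "Pre-existing facial lesions on arrival in the intensive care unit on the path of the endotracheal tube fixation". For patients who arrive intubated, the Inclusion text says this can be checked when the incoming fixation is replaced by the study system.

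D0 is worded twice within section 4.3. Under Inclusion: "D0 is defined as the first day of the study fixation system of the ETT". Under Follow-up, the photos run "from the day of the first fixation change = D0 until D10".

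If the expert reading is missing, section 6.2.5 substitutes the nurse's assessment. The nurse records presence or absence daily, and the study schedule starts that survey at D0.

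**The concern.** Appearance needs a reference point; presence does not. Followed literally, the expert instruction makes a lesion seen on the D0 photo a primary event, even if it came from the intubation itself or from an earlier fixation. Such events say nothing about the device under test. If they are equally common in both arms they dilute the contrast. If they are not, they bias it.

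The two wordings of D0 raise a separate problem, namely what the baseline photo shows. If it is taken at the first change of a study fixation already in place, it is a post-exposure image and cannot serve as a clean reference.

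**Working it through.** **Endpoint against adjudication rule**

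| Place in the protocol | What is recorded | Reference to D0 |
|---|---|---|
| 2.1.2 Primary endpoint | appearance | implied by the word |
| 4.3 Inclusion, admission photo | reason for an initial picture | baseline reasoning, not carried into a rule |
| 4.3 Follow-up, expert task | presence, D0 to D10 | D0 is inside the window |
| 4.5.1 Adjudication Committee | presence or absence | none |
| 6.2.5 Missing data, nurse fallback | nurse's presence or absence, from D0 | none |

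**What the non-inclusion criterion leaves.** It covers lesions at ICU arrival, on the fixation path, that staff recognise. Three groups can remain: peri-oral lesions off the path; lesions missed at the bedside but visible to the experts; and lesions that arise after ICU arrival and before the study fixation is placed.

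**The two D0 wordings.**
- Patient admitted intubated: the first fixation change is the installation of the study system, so the two definitions can coincide.
- Patient intubated in the ICU: the study system is used from the start of ventilation, and the first change comes later, up to about a day. The second definition then moves the window and puts the D0 photo after exposure.
- Section 7.8.2 places the second photo on Day 1, at a fixation change. That fits the Inclusion definition better.

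**Illustration of size.** Inputs from section 6.2.2: "With 90% power and 5% alpha risk", "35% of patients with a 'cord and sleeve' fixation system" against 20% with tape, intra-class correlation 0.10, inter-class correlation 0.05, 16 centres, 24 patients per centre and period. A two-sided test is assumed, as the section does not state sidedness.

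The plan's own figure first:
- Design effect = 1 + (24 − 1) × 0.10 − 24 × 0.05 = 2.10.
- Individually randomised size per arm, unpooled variance: (1.960 + 1.282)² × (0.35 × 0.65 + 0.20 × 0.80) / 0.15² = 181. Pooled variance gives 185.
- Unpooled: 181 × 2.10 = 380 per arm, 760 in total, 23.75 per centre and period. Pooled: 185 × 2.10 = 388.5 per arm, 777 in total, 24.3 per centre and period.
- The stated 24 per centre and period (24 × 16 × 2 = 768) lies between these, so the sample size reproduces.

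Now let a share q of included patients, equal in both arms, have a D0 lesion that is counted as an event. Let 35% and 20% be the incident risks in the rest. The observed risks become q + (1 − q) × 0.35 and q + (1 − q) × 0.20, so the difference is (1 − q) × 15 points. With an effective size of 384 / 2.10 = 182.9 per arm, the unpooled power is Φ(difference / SE − 1.960), where SE = √[(p₁(1 − p₁) + p₂(1 − p₂)) / 182.9].

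| q (assumed) | Cord | Tape | Difference, points | Power, unpooled | Power, pooled |
|---|---|---|---|---|---|
| 0 | 35.0% | 20.0% | 15.0 | 90.3% | 89.8% |
| 2% | 36.3% | 21.6% | 14.7 | 88.1% | 87.6% |
| 5% | 38.25% | 24.0% | 14.25 | 84.6% | 84.0% |
| 10% | 41.5% | 28.0% | 13.5 | 78.2% | 77.6% |

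The protocol gives no value for q.

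**The case against.** The best defence is that the protocol already intends a baseline comparison. The endpoint says appearance, the admission photo is justified on baseline grounds, and each expert holds the full series, D0 included. Lesions on the fixation path are screened out. Section 5.2.2 speaks of mucosal as well as skin lesions in the path of fixation, so the criterion need not be confined to skin. Patients transferred intubated from another ICU are also excluded. All of this stands. It narrows the gap and makes a small q plausible, but it does not change the instruction the experts are given.

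The illustration is open to a further objection. The planning rates come from a cited observational study whose lesion definition is not in the document. If that study counted lesions already present, 35% and 20% already include them, and the power loss shown does not follow.

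Four stronger readings are tempting, and the document does not support them.
- A reader might infer that pre-existing lesions definitely count as events. The protocol leaves this open; only the literal rule would count them.
- A reader might infer that the double definition of D0 is what lets lesions predate the device. For patients intubated in the ICU, a lesion found at the first change follows the study fixation.
- A reader might infer that the exclusion works differently in the two arms because the path depends on the device. Both systems wrap the tube at the mouth and pass around the head or neck (section 4.4), and nothing shows that the area checked differs.
- A reader might think the time-to-lesion origin is wrong. Section 6.2.1 states "The time to onset will be calculated from the date of intubation to the date of first lesion onset", in line with the secondary objective and endpoint in section 2.2. It is a consistent choice for a secondary endpoint.

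**Conclusion.** The point holds as an inconsistency in a stated rule for the primary endpoint: the endpoint is appearance, the adjudication is presence from D0, and nothing says how a lesion on the D0 photo is handled. The nurse fallback has the same gap. The two wordings of D0 are a separate ambiguity. They matter for patients intubated in the ICU, where the window can move by about a day and the baseline photo can become post-exposure.

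The size is unknown. The fall in power from about 90% to between 88% and 78% rests on three assumptions: q between 2% and 10%, the same q in both arms, and planning rates that are purely incident. It shows what could be at stake and is not an estimate. The sample size calculation itself is not in question.

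**What to change.** - Use one definition of D0 throughout: the first day of the study fixation, as under Inclusion, which section 7.8.2 fits.
- Name the D0 photo as the reference image. In the Follow-up text and section 4.5.1, have the adjudicators record whether a lesion absent at D0 appears on any D1 to D10 photo.
- Apply the same new-since-D0 rule to the nurse's assessment when it replaces a missing expert reading (section 6.2.5).

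The first two changes belong together. If D0 could still mean the first change, a new-since-D0 rule might discard a lesion that the study fixation caused before that change.

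The cost is a wording change and slightly more adjudication work on photos already in each file. The adjudication rule can be applied to photos already taken; their timing cannot be altered. Where a first-period D0 photo was taken after the study fixation was in place, this should be identified and reported.

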## FIXATUB protocol

- the average duration of ventilation for patients who require invasive respiratory assistance for more than 48 hours
- risk factors for pressure ulcers which are essentially present at the beginning of the management of patients in shock (oedema, sedation, decrease in tissue perfusion, undernutrition, vasopressor treatments)

The follow-up by the nurse's notebook will stop at the final extubation or at the discharge from the ICU if the patient is discharged intubated from the ICU before D28 or at most D28.

|                              |
|------------------------------|
| SCHEDULE OF THE STUDY |
|------------------------------|

| Actions                                                                                             | D0 | D1 | D2 | D3 | D4 | D5 | D6 | D7 | D8 | D9 | D10 | D22 to D27 | D28 |
|-----------------------------------------------------------------------------------------------------|----|----|----|----|----|----|----|----|----|----|-----|------------|-----|
| Inclusion / non-inclusion criteria                                                                  | X  |    |    |    |    |    |    |    |    |    |     |            |     |
| Participation agreement                                                                             | X  |    |    |    |    |    |    |    |    |    |     |            |     |
| Biological assessment for SOFA                                                                      | X  |    |    |    |    |    |    |    |    |    |     |            |     |
| Assessment of peri-oral lesions:                                                             |    |    |    |    |    |    |    |    |    |    |     |            |     |
| ▮ Paramedical examination (peri-oral lesion survey)                                                 | X  | X  | X  | X  | X  | X  | X  | X  | X  | X  | X   | X          | X   |
| ▮ Photographs (during the change of the fixation system)                                            | X  | X  | X  | X  | X  | X  | X  | X  | X  | X  | X   |            |     |
| Collection of endotracheal tube mobilizations                                                       | X  | X  | X  | X  | X  | X  | X  | X  | X  | X  | X   | X          | X   |
| Collection of the repositioning of the endotracheal tube                                            | X  | X  | X  | X  | X  | X  | X  | X  | X  | X  | X   | X          | X   |
| Collection of re-intubations                                                                        | X  | X  | X  | X  | X  | X  | X  | X  | X  | X  | X   | X          | X   |
| Collection of adverse events related to the investigation procedure and incidents related to the MD | X  | X  | X  | X  | X  | X  | X  | X  | X  | X  | X   | X          | X   |

#### **4.4. DESCRIPTION AND JUSTIFICATION OF THE INTERVENTION STUDIED**

The FIXATUB study is a cluster and crossover randomization study. Patients will be included over 2 periods of 12 months. The timing of both periods (period with the use of the elastic adhesive tape and period with the use of the cord associated with a protective sheath) will be randomly assigned for each center. The sponsor will provide the fixation systems for each period.

There are 3 cord + sheath type fastening systems currently available:

Teleflex® ETT fixation straps, Int'air® medical straps and CairLGL® fixation laces. All 3 are made of cotton tape and a flexible PVC protective sheath and are all 3 classified as MD class 1 non-sterile. No data is available to evaluate the superiority of one of these sheaths.

Each center provided us with their annual consumption of ETT fixation systems in order to obtain a precise evaluation of the quantity of devices required for the project. The quantity of sheaths required being important and the sheath being more expensive than the adhesive elastic band, we will proceed to an "adapted" tender procedure for these 3 suppliers and the devices being similar, the least expensive offer will be chosen.

As for the elastic adhesive tape, we will carry out a competition between the various suppliers and will opt for the least expensive.

### **Description of fastening techniques**

#### **Arm A: "elastic adhesive tape**

Fixation by elastic adhesive tape (Tensoplast type adhesive tape):

The elastic band must be cut in 4 and then in 2 in the width to obtain 8 bands. The length obtained will be 62-63 cm and about 1.5 cm wide.

The tape will be attached to the patient's face (opposite side of the endotracheal tube) and then two wraps around the endotracheal tube. The rest of the tape will be attached to the other side of the face (endotracheal tube side).

The plasticized strip will be kept on the adhesive strip the time to pass on the nape of the neck in order not to stick to the hair.

Finally, the end of the adhesive tape will be replaced on the part already attached to the patient.

**Arm B: "cord + sheath**

- 1) Pull the loop (in the middle of the fastener) to loosen it
- 2) Position the loop around the ETT tube from below.
- 3) Pass the PVC part of the fastener through the loop.
- 4) Pull the ends of the cord out of the sheath to tighten the loop around the ETT tube.
- 5) Tie a knot with both ends of the cord so that the fixation systems is secure around the patient's head

Each fixing systems will be changed daily and after soiling or examinations if necessary.

